## Abstract

**Background:**

Filtered cigarettes and vaped nicotine and cannabis negatively affect health and create nonbiodegradable, toxic waste from tobacco, e-cigarette, and cannabis waste (TECW). Creating awareness and action to address this public health issue requires expanded knowledge and understanding of TECW harms and more engagement with regulatory policies to reduce tobacco and cannabis use. This is the first study testing an intervention to modify TECW knowledge, perceptions, and behavior, including use of an innovative digital TECW tracking tool.

**Objective:**

This study tests the efficacy of an intervention to modify TECW knowledge, harm perceptions, attitudes, and behaviors regarding smoke- and vape-free university campus policies among young adults. We aim to develop an evidence-based educational intervention for use in community programs to address TECW.

**Methods:**

A 6-week randomized controlled trial was conducted at 2 sites representing the 2 public university systems in California from March 2023 to June 2025 with 406 students (aged 18-25 years) and compared brief tobacco, e-cigarette, and cannabis waste education (TECW Ed) plus tobacco, e-cigarette, and cannabis waste education plus motivational and behavioral support (TECW Ed+) with brief education only about TECW (TECW Ed). Participants were randomized 1:1 to each treatment group, stratified by site and tobacco or cannabis use status. Outcome measures include changes in knowledge, harm perceptions, regulatory attitudes, and behaviors regarding TECW, and engagement with smoke- and vape-free policies. Planned statistical analyses include models to assess knowledge, perceptions, and attitudes at weeks 2, 6, and 26 versus group, time, and a group × time interaction, controlling for site, tobacco or cannabis use status, demographics, and baseline level of outcomes. In addition, TECW Ed+ versus TECW Ed group comparison on mean number of Tracker reports between baseline and 6 weeks, and group comparison on mean engagement score at 6 weeks, will be conducted.

**Results:**

Data were collected from March 2023 to June 2025. Data analysis is expected to begin in late 2025, with final results anticipated for publication in summer 2026. Results will determine if brief educational videos accompanied by enhanced motivational and behavioral support increase knowledge of TECW’s environmental impact and change perceptions about cigarettes and vape products. We will determine whether such enhanced education increases engagement in smoke- and vape-free regulatory acceptance and improves outcomes of regulatory policies. This trial will be the first to test an intervention to modify tobacco and cannabis waste perceptions and behavior.

**Conclusions:**

This trial aims to determine whether additional motivational and behavioral support will change young-adult college students’ current knowledge of TECW and whether such support will motivate them to engage with regulatory policies to reduce TECW. If successful, scaling up this intervention may mobilize a large population of young adults to understand and advocate for policies that protect individual and environmental health.

**Trial Registration:**

ClinicalTrials.gov NCT05751369; https://clinicaltrials.gov/study/NCT05751369

**International Registered Report Identifier (IRRID):**

DERR1-10.2196/79525

## Introduction

### Background and Rationale

The global toxic, nonbiodegradable environmental waste from tobacco, e-cigarette, and cannabis waste (TECW) products is a pressing public health issue [1-4]. Upstream policy approaches [5] to address this increasingly recognized waste problem [6-11], such as banning sales of filtered cigarettes [12] and naming them as single-use plastics that may be addressed in a proposed international plastic treaty [13], are important for both environmental and human health reasons [14]. Awareness of the environmental impacts of e-cigarette [1,2,15-19] and cannabis vape products is also growing [2,19-22]. According to the Environmental Protection Agency (EPA), vape products cannot be safely discarded in household trash or recycled; they meet the definition of “hazardous waste.” Many consumers are unaware of this designation, but the EPA has provided guidance to separate batteries from other vape product components that are to be disposed of as municipal hazardous waste [23]. Furthermore, single-use or “disposable” vape products are not designed to be safely disassembled [24].

Disposable nicotine vape products are the most commonly sold [25] and used products in the United States [26], creating a growing environmental challenge [24]. In addition to fires caused by improper disposal of the lithium-ion batteries in vape products, the high-carbon impacts of vape product manufacturing are of concern [27]. The majority of young adults who use disposable nicotine vape products report throwing them in the trash when empty [24]. This provides an estimated 150 million disposable vapes (with potentially recoverable lithium) deposited annually in US landfills [27]. Nearly a quarter of young adults who use vape products report saving the empty products, which also presents a safety issue [24]. There have been no studies to our knowledge on disposal methods for cannabis vape products.

Cultivating public and political support for legislative and regulatory interventions for TECW requires increasing knowledge and modifying perceptions of TECW, and increasing public engagement with policies that can reduce use of tobacco and cannabis products [28]. Research is required on how to influence behaviors that support TECW regulatory policies. To date, there have been 2 observational studies on cigarette butt waste, which both showed that education promotes positive attitudes and behaviors regarding TECW regulations [28,29]. There has not yet been specific research conducted on interventions to increase knowledge, perceptions, and policy engagement on e-cigarette or cannabis product waste. A randomized controlled trial will provide important evidence on the efficacy of such interventions to address TECW, especially among young persons who generally are more engaged on environmental issues.

### Study Objectives

This study tests the administration of tobacco, e-cigarette, and cannabis waste education plus motivational and behavioral support (TECW Ed+) versus tobacco, e-cigarette, and cannabis waste education (TECW Ed) only on TECW among college-attending young adults (aged 18-25 years) to increase their engagement on TECW policy implementation. Brief education is standard of care in university settings, and given our finding that awareness of a technological resource is not sufficient for many people to use it [30], we sought to determine whether the addition of motivational enhancement and behavioral support to education would elicit action.

Outcomes include change in TECW knowledge, harm perceptions, attitudes toward regulation, and smoke- and vape-free regulatory policy engagement. Our overall goal is to identify an evidence-based educational intervention to address TECW, based on environmental concerns [31].

Such interventions are particularly relevant among young people, who are the critical stakeholders in planetary stewardship [32]. Students in California public universities are an important constituency for tobacco-related research given that the 23-institution California State University system and the 10-institution University of California system have 100% smoke- and vape-free campus policies, albeit with persistent policy violations [33]. Compliance issues at California public universities and colleges are emblematic of a broader smoke- and vape-free policy compliance problem at universities [34-36].

### Overview and Trial Design

This is a parallel randomized controlled trial at 2 California universities (1 University of California and 1 California State University) in which a digital TECW Tracker was previously deployed for reporting locations of smoking, vaping, and related waste on campus [30,37]. We enrolled 406 young adult students in a 6-week trial and randomly assigned them 1:1, stratified by site and tobacco or cannabis use status, to usual education only about TECW (TECW Ed) or to receiving the same education about TECW plus motivational enhancement and behavioral support for reporting TECW (TECW Ed+). Changes in individual-level and environmental outcomes are evaluated through repeated assessments at baseline, week 2, week 6, and week 26. Check-in text messages only are provided at weeks 1 and 4.

The guiding framework for this study is social cognitive theory [38,39]. in which behavior is conceptualized as the product of individual-level attitudes and perceptions and social structures that facilitate behavior change. In this study, we use motivational enhancement [40-47], goal setting [48-54], and problem-solving applications [55-60] as developed in our previous trial [61]. Our intervention was designed to address both individual-level attitudes and perceptions and social-level factors through the application of motivational enhancement, which is built around 4 main processes, carried out in a spirit of collaboration, respect, and support for the participant’s autonomy [54]. The first process, engaging, reflects fundamental communication principles and highlights the importance of empathy in establishing trust and rapport. The second process, focusing, involves working with participants to identify and agree on a topic for exploration. The third process, evoking motivation, is directed at drawing out and reinforcing participants’ own internal motivations for change. The fourth process, planning, guides participants in developing and implementing concrete steps toward their goals. The intervention protocol, in which motivational enhancement, goal setting, and problem solving were used to evoke changes in individual- and social-level factors per social cognitive theory, was adapted from one target behavior [61] to another (using TECW Tracker).

## Methods

### Ethical Considerations

The study was reviewed and approved by the Institutional Review Board at Site 1 (#1896205-1) on April 12, 2022. The study was reviewed and approved as exempt by the Institutional Review Board at Site 2 (#1952501-1) on September 2, 2022. Enrollment began on March 1, 2023, and concluded on October 15, 2024.

The informed consent form is delivered to participants by an emailed link in Research Electronic Data Capture (REDCap; Vanderbilt University), along with a link to schedule their baseline visit. The consent form asked, “Would you like to proceed with this study?” using a forced-choice question with two options: I do not wish to proceed with this study or I wish to proceed with this study. Written consent is provided through a typed name with acknowledgment of being aged 18 years or older, of having read and understood the study description, and that they may withdraw at any time. REDCap records the date of consent form completion.

At the beginning of the baseline visit, a description of the study, requirements, and compensation is reviewed; there is an opportunity to ask questions, and participants are asked whether they wish to proceed with the study. Any participants who have not completed the consent form prior to the visit are provided as much time as they need to read the form in a breakout room at the beginning of the visit.

Participants receive up to US $110 for participating in the study: US $25 for attending the baseline, week 2, and week 6 visits, and US $35 for the month 6 visit (Figure 1).

**Figure 1 figure1:**
[figure not shown]
Visit flow.

### Study Setting

The study is conducted in San Diego, California, United States (Site 1), and Davis, California, United States (Site 2). A project coordinator at Site 1 is responsible for participant recruitment and enrollment at both campuses and supervises Site 1–based research assistants. The intervention and assessments are delivered remotely by research assistants at Site 1 to participants at both sites. Participant education and TECW Ed+ group interaction occur over Zoom (Zoom Video Communications, Inc) as a one-to-one session with a research assistant. This method aligns with new norms for synchronous remote participation in university settings. Participants are provided links to surveys and forms in the Zoom chat and are placed in a breakout room to complete them. They are instructed to use the “ask for help” function or rejoin the main Zoom room with questions about the survey. The project coordinator reviews Tracker data and supervises staff at each site who conduct environmental scans and document TECW identified through the Tracker at both campuses.

### Eligibility Criteria

#### Inclusion Criteria

Study eligibility requirements include being a current student on the main campus of Site 1 or 2, attending class on the main campus at least once per week, having at least 6 months remaining until graduation, being aged between 18 and 25 years, English fluency, having a smart phone with location services enabled for apps, having regular access to a computer or tablet with sufficient Wi-Fi and a private space in which to complete remote study visits, and willingness to have the camera turned on during remote study visits.

#### Exclusion Criteria

The only exclusion criterion is prior study participation.

### Intervention Description

#### Overview

Both groups receive education about TECW at baseline and week 2 visits by viewing videos and receiving a link to the TECW Tracker at baseline and week 2. The intervention group receives education plus motivational enhancement and behavioral support for using the TECW Tracker. Both groups receive a check-in text at week 1 and week 4 containing a brief assessment and a reminder for their next study visit. The intervention group’s text includes feedback about the positive environmental impact of making TECW reports and offers assistance with the Tracker if no reports had been made (Figure 2).

**Figure 2 figure2:**
[figure not shown]
Intervention and assessment schedule.

#### Education

Baseline education includes an overview of waste produced by vaping products used for tobacco and cannabis, their impact on the environment, and the role of tobacco and cannabis product manufacturers in TECW mitigation. This material is provided by a brief video from the California Youth Advocacy Network [62]. Week 2 education includes an overview of waste produced by cigarette smoking and the environmental impact of discarded butts. Tobacco Free CA provides brief videos [63,64]. The TECW Tracker is provided as a tool to identify TECW on the campus grounds; this then prompts TECW removal by research staff. The web link and QR code for the TECW Tracker app are provided, and participants are instructed to enter their study ID numbers when making a report.

The TECW Tracker is a digital tool that has been available since 2019 at Sites 1 and 2 to report smoking, vaping, and related waste on Site 1 and 2 campuses [30,37]. Tobacco Tracker provides three types of reports: (1) smoking- or vaping-related litter, (2) smoking or vaping, and (3) “looks good–no smoking or vaping or related litter.” Reports of litter from smoking or vaping allow identification of the source as cigarette butt, cigarette packaging, e-cigarette material (ie, pod, hardware), marijuana packaging, or other (select all that apply). Images of these litter types are included. Reports of smoking or vaping allow identification of the source as cigarette, e-cigarette or JUUL, marijuana (including blunts), do not know, or other; images of these products are embedded within the app. Reports of “looks good–no smoking or vaping or related litter” provide a way to monitor Tracker usage independent of problems and the capacity to measure improvement over time.

#### Mitigation of TECW

The project manager creates weekly mitigation assignments for site staff at each campus to address reports. Site staff conduct a 30-minute environmental scan of the location, collect TECW while wearing protective equipment, classify and document each piece of waste, and dispose of it properly. Each week, a randomly selected campus location is scanned for 60 minutes, and TECW is mitigated by site staff as described above.

#### Motivational Enhancement and Behavioral Support

Each study visit in which education is provided (baseline and week 2) contains additional motivational enhancement or behavioral support for the TECW Ed+ group. Each text message (week 1 and week 4) provides a brief assessment and reminder of the next study visit as well as additional motivational enhancement and behavioral support for the TECW Ed+ group. The week 6 visit provides another motivational booster to the TECW Ed+ group. Table 1 presents the components and timing of the motivational enhancement and behavioral support.

**Table 1 table1:** Timing of motivational enhancement and behavioral support components.

Component	Baseline	Week 1	Week 2	Week 4	Week 6
Discuss video takeaways	✓		✓		
Discuss values and connect to Tracker	✓				
Instruction in using TECW^a^ Tracker	✓		As-needed^b^		
Offer assistance with using Tracker		As-needed^b^		As-needed^b^	
Motivation and confidence for using Tracker	✓				
Action planning for using Tracker	✓		✓		
Summary of Tracker reports and why reporting is useful		✓	✓	✓	✓

^a^TECW: tobacco, e-cigarette, and cannabis waste.

^b^Provided to those who have not made Tracker reports.

### Outcome Measurements

#### TECW Knowledge

Five items assess knowledge of nicotine and cannabis vape-related waste disposal methods (eg, Nicotine pods should be disposed as A. recyclable waste, B. hazardous waste [*correct], C. in normal trash, or D. in other ways) [65,66]. Six items assess knowledge of cigarette waste (eg, What is the main component of commercially sold cigarettes? A. cotton, B. paper, C. plastic [*correct], D. cork, or E. other [14]. Two general questions assessed biodegradability and recommended actions for dealing with TECW. A percent correct score is yielded for knowledge of vape-related and cigarette waste aligning with educational content at the baseline and week 2 visits, respectively.

#### TECW Perceptions

Six items assess agreement with various statements about cigarette and electronic devices used to vape nicotine and cannabis and their environmental impact including biodegradability; harm to the environment, animals, and sea life; and danger if thrown in trash [67,68], on a 5-point scale (strongly disagree to strongly agree). Participants are also asked how often they have noticed TECW in the past 30 days, which product type, and whether occurrences were on or off campus.

#### Regulatory Attitudes

Two items assess regulatory attitudes, including statements about whether various products (eg, cigarette filters, disposable products for vaping, pods or cartridges) should be included in bans of single-use plastic products. Response options range on a 5-point scale from strongly disagree to strongly agree. Tobacco manufacturer responsibility is assessed with items: How much responsibility do you think each of the following groups has for creating the problem of cigarette butt litter and should have for fixing the problem of cigarette butt litter? Groups include smokers, cigarette companies, city councils, and the government. Response options include none at all, a little, a moderate amount, and a great deal [67]. These same items are used to assess manufacturer responsibility for products used to vape nicotine and cannabis. While it may be impossible to distinguish whether vaping-related waste is from tobacco or cannabis, these items are assessed separately for tobacco and cannabis given different regulatory processes.

#### TECW Tracker Use

Awareness of a tool to report TECW on campus and use of the tool is assessed with yes or no questions [30]. Participant Tracker use is also measured objectively based on participant ID–linked TECW Tracker usage data.

#### Engagement in Smoke- and Vape-Free Regulatory Behavior

Engagement in smoke- and vape-free regulatory behavior is assessed with participant behaviors: (1) inform someone smoking or vaping on campus about the environmental impact of TECW, (2) inform someone smoking or vaping on campus about our smoke- and vape-free policy, (3) inform someone smoking or vaping on campus about how to properly dispose of TECW, (4) inform someone smoking or vaping on campus about a resource to quit smoking or vaping, (5) report TECW on campus, (6) report smoking or vaping on campus, and (7) volunteer (provide education, outreach, or clean-up) for campus smoke- and vape-free campus initiatives [30]. These items are rated from 1 (never expect to) to 5 (have already been doing) based on the transtheoretical model of behavior change [69].

#### Secondary Behaviors

To understand any broader impact of the intervention, related behaviors such as off-campus TECW advocacy are assessed; additionally, among tobacco users, proper disposal of e-waste and cessation are evaluated as secondary outcomes. The engagement in smoke- and vape-free regulatory behaviors is modified to “off campus” to assess this, and items about usual methods of TECW disposal and past 30-day quit attempts are assessed.

#### Environmental Impact of TECW Campus Intervention

Counts of TECW by product type as well as “looks good” reports are tabulated for each campus location on a weekly basis from the Esri ArcGIS–based TECW Tracker reports from participants and nonparticipants (eg, general campus community) through TECW Tracker. Counts of TECW by product type are also tabulated from objective environmental scans conducted by site staff.

As a secondary outcome, we assess the link between awareness of campus TECW mitigation and behavioral outcomes. Two items to assess this include: “How aware were you of how your Tracker reports were addressed?” (Response options include not at all, a little, moderately, and very aware), and “How satisfied were you with campus actions taken in addressing TECW?” (Response options range from very dissatisfied to very satisfied). An open-ended prompt follows for those who report dissatisfaction.

#### Attributions of Intervention Components

Following the week 6 survey, those in the TECW Ed+ group are administered another survey assessing their attributions of two intervention components: (1) talking with the study team and (2) receiving feedback about actions taken from TECW reports. They rate their agreement with the following three questions on a 5-point scale, ranging from strongly disagree to strongly agree: [Intervention Component]: (1) taught me new information about TECW, (2) increased my desire to do something to reduce TECW, and (3) increased my desire to report TECW.

### Assessment Schedule

Knowledge, perceptions, and regulatory attitudes for vape-related waste are tested before and after receiving education at the baseline visit. Knowledge, perceptions, and regulatory attitudes for cigarette waste are tested before and after receiving education at the week 2 visit. Knowledge, perceptions, and regulatory attitudes for vape-related waste and cigarette waste are retested at the week 6 and week 26 visits (Figure 2).

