### Assignment of Interventions: Allocation

After completing the baseline survey, participants at each site are randomized 1:1 to the two groups (TECW Ed or TECW Ed+) in blocks stratified by tobacco or cannabis user status (any use in the past 30 days: yes or no) by the project coordinator using REDCap, based on randomization tables created by the study statistician with computer-generated random numbers.

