### Statistical Methods

#### Primary Outcome

The primary outcome is change in knowledge, perceptions, and attitudes. The hypothesis that the TECW Ed+ group will demonstrate a significant increase in TECW knowledge, harm perceptions, and regulatory attitudes, and that the TECW Ed group will be noninferior to the TECW Ed+ group in these outcomes by a margin of half an SD, will be tested as follows. We will compute mean scores for change in knowledge, change in harm perception, and change in belief in each group along with 2-sided 95% CIs; a CI entirely above 0 indicates a statistically significant increase at the 5% level (2-sided). In addition, for each of these measures, we will compute the difference between the TECW Ed+ group and the TECW Ed group mean scores, along with a 1-sided 97.5% CI; a CI entirely below 0.5 SD indicates noninferiority of the TECW Ed group within a 0.5 SD margin at the 0.025 level (1-sided). We will also construct mixed-effects repeated measures models to assess knowledge, perceptions, and belief outcomes at weeks 2, 6, and 26 versus group, time, and a group × time interaction, controlling for site, tobacco or cannabis use status, demographics, and baseline level of the outcome variable.

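### The assessment schedule does not fit the primary model: cigarette-waste outcomes have no listed pre-randomisation measure and vape outcomes no listed week-2 measure

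*Protocol article*

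**What the plan says.** The Assessment Schedule section splits the primary measures by product. For vape: "Knowledge, perceptions, and regulatory attitudes for vape-related waste are tested before and after receiving education at the baseline visit". For cigarettes: "Knowledge, perceptions, and regulatory attitudes for cigarette waste are tested before and after receiving education at the week 2 visit". Both sets "are retested at the week 6 and week 26 visits". No week-2 vape test and no baseline-visit cigarette test is listed.

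The Primary Outcome section under Statistical Methods makes no such split. It plans mean change scores within each arm, a between-arm difference tested against a 0.5 SD noninferiority margin, and a mixed model "to assess knowledge, perceptions, and belief outcomes at weeks 2, 6, and 26 versus group, time" and their interaction, "controlling for site, tobacco or cannabis use status, demographics, and baseline level of the outcome variable". It does not say from which survey change is measured.

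On timing, the Allocation section states: "After completing the baseline survey, participants at each site are randomized 1:1". On what Ed+ receives before the week-2 presurvey, the section on motivational and behavioral support states: "Each study visit in which education is provided (baseline and week 2) contains additional motivational enhancement or behavioral support for the TECW Ed+ group". Table 1 and the Intervention Overview add an Ed+ text at week 1 that summarises Tracker reports and their usefulness.

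**The concern.** Two current sections disagree about the data that feed the primary analysis. A model with a week-2 response needs a week-2 measure, and the schedule lists none for vape. A model adjusted for baseline level needs a baseline measure, and the schedule lists none for cigarette waste.

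The cigarette gap matters more. The nearest substitute for a baseline is the week-2 presurvey. It precedes the cigarette videos but follows randomisation, the Ed+ session at the baseline visit and the week-1 Ed+ text. If Ed+ has already moved these items, subtracting or conditioning on the presurvey takes that part of the effect out of the contrast. The test asks whether Ed is no worse than Ed+ by 0.5 SD, so shrinking Ed+ minus Ed makes success easier to declare.

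**Working it through.** **1. Schedule against model** (Assessment Schedule; Primary Outcome)

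| | Pre-randomisation value | Week 2 | Week 6 | Week 26 |
|---|---|---|---|---|
| Model requires | yes | yes | yes | yes |
| Vape items, as listed | yes (baseline presurvey) | none | yes | yes |
| Cigarette items, as listed | none | pre and post | yes | yes |

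For vape, week 6 minus baseline presurvey is computable. A baseline-adjusted random-intercept model with responses at weeks 6 and 26 was fitted to simulated data (190 per arm) and converged. What is lost is the week-2 level and its group × time term.

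**2. The plan's own figure**

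Sample Size assumes 380 at week 6, so 190 per arm, and claims more than 95% power for noninferiority within 0.5 SD at one-sided 0.025. In SD units the standard error of the difference is sqrt(2/190) = 0.1026. With no true difference, power = Φ(0.5/0.1026 − 1.96) = 99.8%. With 170 per arm at week 26 it is 99.6%. The claim reproduces and is unaffected by this point.

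**3. Effect of using the week-2 presurvey as the cigarette baseline**

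Inputs that are not in the documents and are assumed:
- d, the Ed+ minus Ed shift already present at the week-2 presurvey: 0 to 0.3 SD.
- r, the correlation of that presurvey with the week-6 score: 0.3 to 0.7.
- The true week-6 difference equals the 0.5 SD margin, so noninferiority should be declared 2.5% of the time. SD is that of the raw score, equal at both times.

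The change-score contrast becomes 0.5 − d, with SD multiplier sqrt(2(1 − r)). The adjusted contrast becomes 0.5 − r·d, with multiplier sqrt(1 − r²). Then:

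- Change score: P(noninferior) = Φ(d / [0.1026·sqrt(2(1 − r))] − 1.96)
- Adjusted: P(noninferior) = Φ(r·d / [0.1026·sqrt(1 − r²)] − 1.96)

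Worked case, d = 0.1 and r = 0.5:
- Change score: Φ(0.1/0.1026 − 1.96) = Φ(−0.985) = 16.2%.
- Adjusted: Φ(0.05/(0.1026 × 0.866) − 1.96) = Φ(−1.397) = 8.1%.

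| d | r | Change score | Adjusted |
|---|---|---|---|
| 0 | any | 2.5% | 2.5% |
| 0.05 | 0.5 | 7.0% | 4.7% |
| 0.1 | 0.3 | 12.8% | 4.9% |
| 0.1 | 0.5 | 16.2% | 8.1% |
| 0.1 | 0.7 | 24.1% | 15.8% |
| 0.2 | 0.5 | 49.6% | 20.2% |
| 0.3 | 0.5 | 83.2% | 39.3% |

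Comparing week-6 scores directly between arms carries no such bias, missing data aside, because nothing measured after randomisation is subtracted or conditioned on.

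**The case against.** Four points have weight.

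- **The plan does not name the week-2 presurvey as the cigarette baseline.** It leaves the reference undefined, and an unseen SAP may define it. That stands as a limit on the bias claim. It does not remove the mismatch, because both sections are current and the model as written needs measures that the schedule does not list.
- **An early shift may be negligible.** The Education section places vape content at baseline and the cigarette videos at week 2, and both arms receive the Tracker link at baseline. For cigarette knowledge, d near zero is quite possible. It is less safe for perceptions and regulatory attitudes: the baseline video covers manufacturers' role in mitigation, and the Tracker, in which Ed+ is instructed, shows images of cigarette litter. The documents give no size.
- **The false-noninferiority rates describe the boundary case**, a true difference exactly at the margin. That is the usual place to check a type I error, but the rates are not forecasts for this trial.
- **The schedule may be incomplete.** It refers to Figure 2, which is not available here. The Overview and Trial Design section speaks of "repeated assessments at baseline, week 2, week 6, and week 26" without a product split. If cigarette items were asked at baseline, the Assessment Schedule is what needs correcting.

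A reader might infer more: that the vape analyses cannot be run, that the cigarette results are biased, or that half of every primary domain is affected. The documents support none of these. The vape change to week 6 starts from a pre-randomisation value. The cigarette bias needs both the presurvey as reference and an early Ed+ effect. As for the half, knowledge has 5 vape, 6 cigarette and 2 general items, and the perception items are not broken down by product.

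**Conclusion.** The mismatch is real and concerns the primary outcome. For vape it is limited to the week-2 level of the mixed model; the baseline-to-week-6 change is untouched. For cigarette waste, the plan leaves open a between-arm analysis that uses a post-randomisation value as its baseline.

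If that reading is adopted and Ed+ has moved the items by 0.1 SD before week 2, the one-sided error at the margin rises from 2.5% to 12.8-24.1% with change scores, or to 4.9-15.8% with adjustment. These figures rest on 190 per arm and an assumed r of 0.3 to 0.7. With no early shift the error stays at 2.5%. The structural mismatch is certain on the listed schedule; the bias is conditional and its size unknown.

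**What to change.** Reconcile the Assessment Schedule, the Primary Outcome section and Figure 2, and state reference and response times by product before outcomes are examined by arm.

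- **Vape:** baseline presurvey as covariate; responses at weeks 6 and 26. The baseline postsurvey may be added as a response.
- **Cigarette, between arms:** for the noninferiority test and the mixed model, compare week-6 and week-26 scores, adjusting only for pre-randomisation variables: site, use status, demographics and the baseline vape score of the same domain. Do not adjust for the week-2 presurvey or analyse change from it. Report the presurvey by arm so that readers can see whether an early difference existed.
- **Cigarette, within arm:** keep the change from the week-2 presurvey to week 6 with its 95% CI. It tests the planned hypothesis of an increase and needs no pre-randomisation value, so there is no reason to reduce it to description.

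If Figure 2 or the survey forms show that cigarette items were asked before randomisation, correct the schedule and use that value as the covariate.

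No new data are needed. The cost is some precision in the cigarette comparisons, because the vape score is a weaker covariate than a same-item baseline. The noninferiority test can bear this: the 99.8% power above assumes no covariate adjustment.
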